# OBJECTIVES AND OUTCOME MEASURES/ENDPOINTS

| **Objectives** | **Outcome Measures/Endpoints** |
| --- | --- |
| **Primary Objective** To assess the impact of group drumming on anxiety and depression in mental health service users | Hospital Anxiety and Depression Scale (HADS) |
| **Secondary Objectives**  To assess the impact of group drumming on:  Wellbeing  Social resilience  Psychological stress  Neuroendocrine stress  Inflammatory immune response  To compare whether 6 or 10 weeks is more effective | Warwick-Edinburgh Mental Wellbeing Scale (WEMWBS)  Connor-Davidson Social Resilience Scale (CD-RISC)  Perceived Stress Scale (PSS  Cortisol (through saliva samples)  Cytokines (through saliva samples)  Comparison of results between baseline and week 6 and week 10 |

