## Subsequent Assessment

The data collection carried out in week 1 will be repeated in weeks 6 and 10. For the experimental group, this will also be repeated 3 months following the end of the intervention.

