# STATISTICS AND ANALYSIS

## Description of Statistical Methods

Data will be analysed using IBM SPSS Version 22.0.1 (SPSS, Chicago, IL). We will compare results using repeated measures analysis of variance (ANOVAs) with planned simple contrasts, both within and between subjects. Differences with a resultant p value of <.05 will be considered significant. In the event that data is non-parametric, we will use Kruskall-Wallis one-way analysis of variance. However, if biological data is non-parametric, we will attempt to transform prior to analysing parametrically.

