## The Number of Participants

Sample size calculations using an alpha of 0.05, power of 0.8 and an effect size of 0.25 (2 groups, 3 timepoints) suggest an overall total of 28 participants will be required (14 per group). For the control group, in order to allow for drop-outs of 30%, 20 participants will be targeted for recruitment. For the experimental group, because of the range of biological markers being tested, we will match sample size with our preliminary study, and so 39 participants will be recruited. Recruitment will be continued until these targets are reached before being closed one week before the drumming starts.

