## Analysis of Outcome Measures/Endpoints

Psychological scale scores will be measured and data inputed to IBM SPSS Version 22.0.1. Change from baseline and within groups will be measured. Saliva samples will be shipped to Aeirtec Laboratories and analysed using multiplex ELISAs.

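### The only non-parametric fallback, Kruskal-Wallis, does not fit the within-subject comparisons, and its input for the between-group comparison is not stated

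*Protocol*

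**What the plan says.** Section 8.1 (Description of Statistical Methods) sets the main analysis: "We will compare results using repeated measures analysis of variance (ANOVAs) with planned simple contrasts, both within and between subjects". The fallback follows: "In the event that data is non-parametric, we will use Kruskall-Wallis one-way analysis of variance". One exception is made: "However, if biological data is non-parametric, we will attempt to transform prior to analysing parametrically". No other rank method is named anywhere in the protocol.

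The design is longitudinal. Under Subsequent Assessment, "The data collection carried out in week 1 will be repeated in weeks 6 and 10", with a further assessment three months after the end of the intervention in the experimental group only. The secondary objective of comparing 6 with 10 weeks has as its outcome "Comparison of results between baseline and week 6 and week 10". The primary objective is "To assess the impact of group drumming on anxiety and depression in mental health service users", measured by HADS. Section 8.3 (Analysis of Outcome Measures/Endpoints) adds: "Change from baseline and within groups will be measured". That sentence is not tied to the fallback.

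**The concern.** The main analysis answers two kinds of question: how scores move over time in the same people, and whether that movement differs between groups. The fallback is a one-way test for independent samples.

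- **Within subjects.** Entering the timepoints as if they were separate samples discards the pairing. The variation between people stays in the error term, so the test becomes very conservative and loses power.
- **Between groups.** The result depends on what is entered. Raw week-6 or week-10 scores carry any difference that was there at the start. These groups are not randomised: the controls are people already attending community social groups, so a baseline difference is foreseeable. A standing gap can then look like an effect, or hide one.

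The exception for biological data leaves the fallback to govern mainly the self-report scales, and hence the primary endpoint. If the input and the test are settled only once the data are known to be awkward, the choice of primary test is open at the wrong moment.

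**Working it through.** **1. Which test the trial was sized for.** Section 8.2 gives "Sample size calculations using an alpha of 0.05, power of 0.8 and an effect size of 0.25 (2 groups, 3 timepoints") and a total of 28. Read the effect size as Cohen's f and assume a correlation ρ = 0.5 between timepoints (the protocol gives none), with sphericity. For the within-subject or group-by-time test:

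- λ = f²·N·m/(1 − ρ) = 0.0625 × 28 × 3 / 0.5 = 10.5
- df = 2 and (28 − 2) × 2 = 52; power = 0.812

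So 28 reproduces. A between-group main effect with the same f and ρ would need 86. The plan's sample size therefore matches a test on time or on group-by-time, which Kruskal-Wallis on raw scores does not supply.

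**2. Inputs for the illustration.** Section 8.2 gives targets of 39 and 20. Its 30% drop-out is stated for the controls: 20 × 0.70 = 14. Applying the same rate to the experimental arm is an assumption: 39 × 0.70 = 27.3, taken as 27. Also assumed: normal data with equal correlation 0.5 or 0.7 between timepoints, a 0.5 SD fall by week 10 (0.25 SD by week 6), and a stable 0.5 SD baseline gap. Each scenario was simulated 3,000 times, so a rate near 30% has a standard error of √(0.3 × 0.7/3000) = 0.8 percentage points.

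**3. Across timepoints in one arm (n = 27).**

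| | ρ = 0.5 | ρ = 0.7 |
|---|---|---|
| Kruskal-Wallis, size (nominal 5%) | 0.3% | 0.0% |
| Kruskal-Wallis, power for 0.5 SD fall | 24% | 18% |
| Friedman, power for 0.5 SD fall | 48% | 69% |

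A closed-form check on the size: with rank correlation r = (6/π)·arcsin(ρ/2), the statistic behaves in large samples like (1 − r) times a chi-square on 2 df. The rejection rate is then exp{−(5.991/2)/(1 − r)}. For ρ = 0.5, r = 0.483 and the rate is 0.3%. For ρ = 0.7, r = 0.683 and the rate is 0.008%. Both agree with the simulation. Friedman held its size at 5.4% to 5.5% in simulations of one arm of 39 (ρ = 0.3 to 0.7).

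**4. Between groups at week 10 (27 v 14), 0.5 SD baseline gap, no difference in change.**

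| | ρ = 0.5 | ρ = 0.7 |
|---|---|---|
| Kruskal-Wallis on raw week-10 score | 29% | 31% |
| Kruskal-Wallis on change from baseline | 4.9% | 5.0% |

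Check on the raw-score row: the shift is 0.5 × √(27 × 14/41) × √(3/π) = 0.5 × 3.036 × 0.977 = 1.48 standard errors, and Φ(1.48 − 1.96) is about 32%. It does not depend on ρ, so the two simulated values differ only by chance. At the full targets, 39 v 20, the simulated rate is 41%.

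**5. What the comparison shows.** The same test on the same data is sound or unsound between groups according to its input, and the protocol does not state the input. Across timepoints no input makes it a paired test.

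**The case against.** Four points deserve weight.

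- **Change scores are a plausible input.** A reader might infer that Kruskal-Wallis cannot assess group differences in change at all. That is not so. With two groups it is equivalent to Mann-Whitney, and on change scores it holds its size at about 5%, even with a baseline gap. Section 8.3 says change from baseline will be measured, so this use may be what was meant. The point stands, and it limits the between-group concern to an unstated input.
- **The primary analysis is not thereby invalid.** A reader might also infer that it is. The planned analysis is repeated measures ANOVA. The fallback matters only if it is triggered, and the within-subject failure costs power without creating false positives.
- **The 29%/31% figure measures baseline imbalance.** Any comparison of raw week-10 scores, parametric or not, would behave in the same way. That is right. The figure shows why the input must be fixed, not a defect peculiar to this test.
- **The detail could sit in a statistical analysis plan.** That holds for the input. It does not hold for the within-subject part, because the protocol already names a method and that method does not suit repeated scores.

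The simulations also use normal data, the setting in which the fallback would not be invoked. They show what ignoring pairing or baseline does. They do not forecast this trial's HADS results, and the documents give no basis for saying how likely the trigger is.

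**Conclusion.** The point holds in this form. The one named fallback is mismatched to the within-subject comparisons in section 8.1 and in the 6-versus-10-week objective. For the between-group comparison it is under-specified: sound on change scores, exposed to baseline differences on raw scores. The within-subject mismatch follows from the text and needs no assumption. The sizes do rest on assumptions: the correlation, the completer numbers, the 0.5 SD fall and the 0.5 SD gap are illustrative. Under them the within-subject fallback has about half the power of Friedman at ρ = 0.5 (24% against 48%) and about a quarter at ρ = 0.7 (18% against 69%). The raw-score comparison has about six times the nominal false-positive rate (29% to 31% against 5%). The documents do not support a claim that the primary analysis as planned is invalid.

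**What to change.** Replace the fallback sentence in section 8.1 with:

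*If model residuals are clearly non-normal, groups will be compared by Mann-Whitney (equivalently two-group Kruskal-Wallis) on change from baseline to week 6 and to week 10, and within-group change over time will be tested by Friedman with Wilcoxon signed-rank contrasts.*

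This keeps repeated measures ANOVA as the main analysis, states the input, gives the within-subject comparisons a paired method, and ties the trigger to residuals instead of an undefined property of the data. The rule for transforming biological data can stay as it is. The cost is one sentence, with no change to recruitment, assessments or sample size. It should be made before the outcome data are examined.

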## The Number of Participants

Sample size calculations using an alpha of 0.05, power of 0.8 and an effect size of 0.25 (2 groups, 3 timepoints) suggest an overall total of 28 participants will be required (14 per group). For the control group, in order to allow for drop-outs of 30%, 20 participants will be targeted for recruitment. For the experimental group, because of the range of biological markers being tested, we will match sample size with our preliminary study, and so 39 participants will be recruited. Recruitment will be continued until these targets are reached before being closed one week before the drumming starts.

## Analysis of Outcome Measures/Endpoints

Psychological scale scores will be measured and data inputed to IBM SPSS Version 22.0.1. Change from baseline and within groups will be measured. Saliva samples will be shipped to Aeirtec Laboratories and analysed using multiplex ELISAs.

# DATA MANAGEMENT

## Access to Data

Data will only be accessible by the immediate study team. However, direct access will be granted to authorised representatives from the Sponsor or host institution for monitoring and/or audit of the study to ensure compliance with regulations.

## Data Recording and Record Keeping

No patient medical records will be accessed for this study. All data will be stored in linked anonymised form so data is not immediately identifiable. Study data will be stored on secure computers only accessible to the study team. For the three-month follow-up, participants will be sent questionnaires to complete in the post, and this contact information will be stored separately from anonymised data.

# QUALITY ASSURANCE PROCEDURES

The study may be monitored, or audited in accordance with the current approved protocol, ICH GCP, relevant regulations and standard operating procedures.

# ETHICAL AND REGULATORY CONSIDERATIONS

## Declaration of Helsinki

The Investigator will ensure that this study is conducted in accordance with the principles of the Declaration of Helsinki.

## ICH Guidelines for Good Clinical Practice

The Investigator will ensure that this study is conducted in full conformity with relevant regulations and with the ICH Guidelines for Good Clinical Practice (CPMP/ICH/135/95) July 1996.

## Approvals

The protocol, informed consent form, participant information sheet and any proposed advertising material will be submitted to the Head of the Centre for Performance Science at the Royal College of Music and the NHS Research Ethics Committee (REC) for written approval. The Investigator will submit and, where necessary, obtain approval from the above parties for all substantial amendments to the original approved documents.

## Reporting

An End of Study notification and final report will be submitted to the same parties and data uploaded to clinicaltrials.gov.

## Participant Confidentiality

Patient data will remain anonymous to the study team throughout the study and there will be no access to patient medical records. Participants will be assigned unique identification codes. All documents will be stored securely and only accessible by study staff and authorised personnel.

# FINANCE AND INSURANCE

## Funding

The study is being funded by the Arts and Humanities Research Council

## Insurance

Royal College of Music has an indemnity and insurance policy that will cover the entire study.

# PUBLICATION POLICY

The Investigators will be involved in reviewing drafts of the manuscripts, abstracts, press releases and any other publications arising from the study. Authors will acknowledge that the study was funded by the Arts and Humanities Research Council. Authorship will be determined in accordance with the ICMJE guidelines and the Vancouver Protocol and other contributors will be acknowledged.

